## Assignment of interventions: blinding

### Who will be blinded {17a}

Participants, researchers, and facilitators will not be blinded, as it is impossible for them not to realize who received the intervention and who did not. Parental consent will be obtained prior to randomization. However, schools must be informed of the intervention schedule in advance to facilitate planning, allocate time for the sessions, and arrange travel. Participants will complete the questionnaires without prior knowledge of the upcoming intervention to minimize potential bias; they will be informed afterward regarding the timing and nature of the next activity.

### Procedure for unblinding if needed {17b}

We will not blind anyone involved in this study; the unblinding procedure is therefore not needed.

## Data collection and management

### Plans for assessment and collection of outcomes {18a}

Outcome measures are self-reported questionnaires and will be answered at baseline (Timepoint 1), immediate post-test (Timepoint 2), and follow-up (Timepoint 3).

Questionnaires are described in detail in Sect. 12.

To ensure data quality, 2 control items are included in the questionnaire (e.g., “mark number 3”). Data from participants who failed both attention checks will be excluded. Research assistants are present during completion of the questionnaires to answer questions and ensure participants’ understanding of the items. Questionnaire data is then inputted into an Excel sheet by the research assistants.

All sessions are video and/or audio recorded, and 10% of sessions are assessed for facilitator’s adherence to the script by trained assessors. The same assessors showed strong interrater reliability during the pilot study in Colombia (manuscript in preparation).

### Plans to promote participant retention and complete follow-up {18b}

The research team is fostering strong, collaborative relationships with participating schools and will provide regular updates on the project’s progress. Schools will be invited to workshops and research presentations to maintain their engagement and interest throughout the study.

All sessions are co-designed by local researchers and young adults to ensure cultural relevance and youth-centred approaches. Activities have been pilot tested and received positive feedback from both adolescent participants and facilitators. To express appreciation and encourage continued participation, participants will receive small gifts and snacks after each session. When possible, alternative catch-up sessions will be arranged within a few days for any participants who are absent on the day of data collection.

Participants who choose to withdraw from the study will be invited to share their reasons, if they feel comfortable doing so. They will also be offered additional resources or referrals to appropriate specialists, as needed.

### Data management {19}

Informed consent will be obtained from parents or guardians, and assent will be obtained from adolescent participants. Self-report questionnaires will be completed on paper. All physical documents will be securely stored in a locked office accessible only to the research team.

Questionnaire responses will be entered into Excel files stored on the secure OneDrive accounts of Universidad del Norte and backed up on Durham University’s servers as soon as possible. To ensure transparency and reproducibility, all data processing and analysis steps will be documented in RStudio. The analysis scripts and anonymized datasets will be made publicly available via the Open Science Framework (OSF).

### Confidentiality {27}

Data will be stored using unique identification codes to link participants’ pre-, post-intervention, and follow-up responses. The file containing the key to these codes will be stored separately from the anonymized research data. Only the research team will have access to personally identifiable information. All analyses and publications will be based solely on anonymized data to ensure participant confidentiality.

### Plans for collection, laboratory evaluation, and storage of biological specimens for genetic or molecular analysis in this trial/future use {33}

Not applicable, we do not collect any biological specimens.

## Statistical methods

### Statistical methods for primary and secondary outcomes {20a}

Data will be analysed using RStudio [30]. First, data will be assessed for completely missing at random using Little’s test (MCAR) [31]. If data is missing at random (MAR), we will employ linear mixed-effects models to examine the effects of the intervention, using the Maximum Likelihood approach. If data is not missing at random, we will employ Multiple Imputation. The number of imputations will be decided based on m≈ %missing (as recommended by [32]). Furthermore, we will run MNAR sensitivity analyses (pattern-mixture/delta) [33].

Each outcome will be analysed using a linear mixed-effects model including the baseline measure of the outcome, gender, and the interaction between gender (boys vs. girls) and group (intervention vs. control) as fixed effects, along with timepoint (baseline, immediate post-test, follow-up). Random intercepts will be included for participant (to account for repeated measures) and nested clustering of classes within schools to reflect the cluster-randomized design. Analyses will be conducted separately for each outcome variable; primary outcomes will be used for confirmatory inference, while secondary and exploratory outcomes will be analysed separately with appropriate multiple-comparison adjustment as required. To estimate effect sizes, we will calculate partial eta squared. Following Cohen’s [34] guidelines, values of 0.01, 0.06, and 0.14 will be interpreted as small, medium, and large effects, respectively [34].

Subgroup analyses will be conducted based on baseline scores for each outcome variable, comparing participants with high versus low initial levels (categorized using median splits of baseline scores). In addition, moderator analyses will include interactions between each moderator and group to examine the potential influence of gender, socioeconomic status (high vs. low), location (urban vs. rural), and school type (state vs. private) on intervention effects.

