### Trial design {8}

In this two-arm cluster-randomized, open-label, controlled superiority trial, we will compare changes in primary and secondary outcomes in participating adolescents randomized to receive either the intervention or a wait-list control condition in a parallel group design over the first 9–12 months of the study. The group allocation ratio is 1:1, clustered by school and stratified by geographical location (urban/rural), socioeconomic position (high/low), and funding status (state/private). Participants in the waitlist control group will receive the intervention after follow-up data collection is concluded.

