### Participant timeline {13}

#### Sample size {14}

The trial aims to detect small between-group effects of our outcomes. The pilot trial in Colombia (*N* = 338) showed that the smallest effect size was approximately *d* = 0.3 (body dissatisfaction in boys); we aimed for a slightly lower effect size of *d* = 0.25. For the primary sample-size calculation, we assumed a two-sided significance level of *α* = 0.05, 80% power (1 − β = 0.80), and equal allocation to two arms (intervention vs. control), yielding 251 participants per arm. Because this trial uses a cluster-randomized design, sample size calculations incorporated clustering effects, including ICC (intraclass correlation coefficient) and DE (design effect), which determines how much the sample size needs to be inflated compared to an individually randomized trial). Based on the pilot trial in Colombia, we assumed an average group size of *m* = 25 and an ICC of 0.046, which requires 529 participants per arm. We allowed for 10% attrition, yielding a sample size of 611 participants and 1250 participants in total (see Table 1 and Fig. 1).

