## Assignment of interventions: allocation

### Sequence generation {16a}

Random blocks will be used to assign participating schools according to their SES (high vs. low) and geographical area (rural vs. urban), resulting in three different blocks: rural/low SES; urban/high SES; urban/low SES. In each block, schools will be randomly assigned to either the intervention or treatment group. The allocation sequence will be determined using computer-generated random numbers from Researchrandomizer.org.

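### Section {20a} names Maximum Likelihood for the confirmatory mixed models of a school-randomised trial; if schools are few, this tends to make group-effect standard errors too small

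*Protocol article*

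**What the plan says.** All references are to the protocol article. Statistical methods {20a} first deals with missing data. If data are missing at random, "we will employ linear mixed-effects models to examine the effects of the intervention, using the Maximum Likelihood approach"; otherwise multiple imputation is used. The next paragraph sets out the model. On the random part it says: "Random intercepts will be included for participant (to account for repeated measures) and nested clustering of classes within schools". It also says that "primary outcomes will be used for confirmatory inference". That paragraph names no estimator, and REML, a reference distribution and a degrees-of-freedom method appear nowhere in the article.

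The design facts that bear on this are:
- Trial design {8}: "The group allocation ratio is 1:1, clustered by school".
- Sequence generation {16a}: schools are allocated within blocks, "resulting in three different blocks: rural/low SES; urban/high SES; urban/low SES".
- Sample size {14}: "we assumed a two-sided significance level of" 0.05, and "we assumed an average group size of" 25 with an ICC of 0.046.
- The number of schools is not stated.

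**The concern.** The group contrast is a comparison of schools, so its standard error depends mainly on the estimated between-school variance. ML estimates that variance without allowing for the fixed effects already estimated at school level; with an intercept and a group effect, it divides by J schools where J − 2 would be unbiased. REML makes that allowance. With many schools the difference is negligible. With few, ML tends to give standard errors that are too small, intervals that are too narrow, and a test that rejects more often than the planned 5%. Both primary outcomes would be affected.

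ML is not needed for the purpose that the sentence serves. REML is also likelihood-based and uses the same incomplete records under missing at random.

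**Working it through.** **Planning figure.** For d = 0.25, two-sided 5% and 80% power, the usual formula gives 252 per arm (stated: 251). The design effect is 1 + (25 − 1) × 0.046 = 2.104, and 251 × 2.104 = 528.1, rounded up to 529 as stated. So 25 is the cluster size that the calculation used.

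**Number of schools (assumption).** 1250 / 25 = 50 groups. One group per school gives 50 schools, two give about 25, and four give about 12. Study setting {9} describes classroom groups of 20–40, so 25 looks like a class size. Four grades are eligible, and the model has "nested clustering of classes within schools to reflect the cluster-randomized design". More than one class per school is therefore plausible, and I take 50, 24 and 12 schools.

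**Type I error, all clustering at school level.** Assume J equal-size schools, two school-level parameters (intercept and group) and one time point. The REML-based statistic follows t with J − 2 degrees of freedom. The ML standard error is smaller by the factor √((J − 2)/J). Hence:
- ML, normal reference: P(|t(J−2)| > 1.96 × √((J−2)/J))
- REML, normal reference: P(|t(J−2)| > 1.96)
- ML, t reference: P(|t(J−2)| > c × √((J−2)/J)), where c is the 97.5% point of t(J−2)

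| Schools J | √((J−2)/J) | c | ML, normal | REML, normal | ML, t(J−2) |
|---|---|---|---|---|---|
| 50 | 0.980 | 2.011 | 6.1% | 5.6% | 5.5% |
| 24 | 0.957 | 2.074 | 7.4% | 6.3% | 6.0% |
| 12 | 0.913 | 2.228 | 10.4% | 7.8% | 6.9% |

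REML with t(J−2) gives 5% by construction.

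**Simulation check.** With 1125 analysed (1250 less 10%), ICC 0.046 and variances not allowed below zero, ML with the normal reference gave 6.0%, 7.5% and 10.3%. ML with t gave 5.4%, 6.0% and 6.8%, and REML with t gave 4.9% to 5.1%. The ML between-school variance averaged 92%, 88% and 80% of its true value; REML averaged 100%.

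**Splitting the excess.** Under the normal reference, ML minus REML is about 0.5 points at 50 schools, 1.1 at 24 and 2.5 at 12. At 12 schools the total excess is 10.4 − 5.0 = 5.4 points, so about half is due to ML and the rest to the normal reference.

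**Moving the clustering to classes.** The model also has a class intercept. Simulating 12 schools with 4 classes each, 1125 analysed, and fitting both variances by ML gives approximately:

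| School ICC | Class ICC | ML, normal | ML, t(J−2) |
|---|---|---|---|
| 0.046 | 0 | 10.3% | 6.9% |
| 0.023 | 0.023 | 9.7% | 6.3% |
| 0.010 | 0.036 | 8.0% | 4.9% |
| 0 | 0.046 | 5.4% | 3.0% |

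The inflation shrinks as the clustering moves from school to class. It disappears under the t reference in the last two rows, and almost disappears under the normal reference in the last.

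**The case against.** The strongest reply concerns what the text commits to. The phrase stands in a missing-data sentence, where it contrasts a likelihood-based model with multiple imputation, while the paragraph that specifies the model is silent on the estimator. The authors may never have meant ML as opposed to REML. This stands as a point about intent. It does not remove the problem, because ML is the only estimator named: an analysis plan that follows the protocol inherits it, and one that uses REML departs from it.

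Second, the larger figures need a normal reference, and the document names no test. The planned partial eta squared is usually built from an F or t statistic, which, if anything, points the other way. Degrees of freedom are also commonly left to the analysis plan, so their absence is not the point here. This stands, and it limits what can be charged to ML. It does not clear ML: with a t reference and all clustering at school level, the error still exceeds 5%.

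Third, if 25 is a class size, then 0.046 describes classmates, and placing all of it at school level is the unfavourable case. If 25 is the school cluster, there are about 50 schools and the error is 6.1% or 5.5%. This also stands.

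A reader might infer that the 5% level will certainly fail and the intervals will certainly be too narrow. The documents do not support that, because the number of schools, the split of the ICC and the reference distribution are all unknown. A reader might also enter the three randomisation blocks and obtain a larger error, but the main model in {20a} does not list them.

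**Conclusion.** The point holds in conditional form. The protocol names an estimator that underestimates the variance on which its randomised comparison rests, and this matters if schools are few. Over 50 to 12 schools, the type I error is at most about 6.1% to 10.4% with a normal reference and 5.5% to 6.9% with a t reference. These limits assume equal-size schools, ICC 0.046 entirely between schools, two school-level parameters and one time point; unequal schools would change them somewhat. Between-class clustering lowers them, in places to 5% or below. It is a worthwhile correction because the remedy costs almost nothing, not because the stated error rate is shown to fail.

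**What to change.** In {20a}, replace the Maximum Likelihood phrase with: *fitted by REML (which uses all available records under MAR), with Kenward-Roger or Satterthwaite degrees of freedom for tests and confidence intervals of group effects*. Keep ML only for comparing fixed-effect structures. Both parts are needed, since REML with a normal reference still gives 5.6% to 7.8% in the table above.

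The cost is one sentence, one software option and slightly wider intervals. The handling of missing data under missing at random is unaffected. The change is best made before the interim analysis of the post-test data described in {21b}.

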## Methods: participants, interventions, and outcomes

### Study setting {9}

This project will run full assessments of the effectiveness of the program with adolescents attending 7th to 10th grade (typically 11–17-year-olds) in urban and rural Northern Colombia. Trained facilitators (paid research assistants) and students will deliver materials during the school day. Schools will be recruited through word of mouth and researcher contacts. All intervention activities are classroom-based and will be delivered to mixed-gender groups of 20–40 participants during class time. Outcome assessments will also be completed during the school day, in classrooms. Materials have been refined based on prior pilot study data with adolescents in the city of Barranquilla (*N* = 338). Quantitative assessments will use a wait-list control design, with outcomes measured at baseline, immediate post-test, and follow-up (9–12 months later). We are using translated and validated scales to assess body image, sociocultural internalization, eating attitudes, and general wellbeing. Additionally, we are in the process of validating scales measuring appearance comparison, curvy ideal internalization, appearance-altering behaviours, and colourism attitudes. All scales have undergone psychometric evaluation and linguistic adaptation to ensure cultural relevance for the Colombian context in a sample of Colombian adults (*N* = 505; *M*_age_ = 21.48, *SD* = 2.96, range 18–30). 

In Colombia, all areas are classified into six socioeconomic strata (*estratos*) based on residents’ income and living conditions. *Estrato* 1 includes the lowest-income households, whereas *Estrato* 6 comprises the highest. This stratification system is used to determine public service subsidies and utility fees: lower strata receive financial assistance for basic services such as electricity and water, while higher strata pay increased rates to support social equity [12].

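### The gender × group test uses random intercepts only, so it is valid only if the girl-boy gap is the same in every school

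*Protocol article*

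**What the plan says.** Three parts of the Protocol article bear on this.

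- **Design.** Trial design {8} states: "The group allocation ratio is 1:1, clustered by school". Study setting {9} says the sessions are "delivered to mixed-gender groups of 20–40 participants during class time". Gender is therefore a pupil-level factor that varies within each randomised unit.
- **Fixed part of the model.** Statistical methods {20a} includes "the interaction between gender (boys vs. girls) and group (intervention vs. control) as fixed effects", and the same section lists gender again among the moderators. The term applies to both primary outcomes and to every other outcome measured in both genders.
- **Random part of the model.** The same section states: "Random intercepts will be included for participant (to account for repeated measures) and nested clustering of classes within schools to reflect the cluster-randomized design". It names no random slope for gender, no robust variance and no degrees-of-freedom method for the interaction.

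**The concern.** With arm randomised by school and gender varying inside schools, gender × group compares the average within-school girl-boy gap between the two arms. The independent replicates of that gap are schools. Its standard error should therefore contain two parts: pupil-level sampling error, and the variation of the true gap from school to school.

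A school or class intercept moves boys and girls by the same amount and drops out of the gap. An intercept-only model thus sets the second part to zero. If the true gap does vary, the standard error is too small and the interaction is found significant too often. At stake is a statement that the programme works differently in boys and girls on media literacy or body dissatisfaction. Such a statement could be challenged as a product of the error term.

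**Working it through.** **Inputs from Sample size {14}.** On the error rate, "we assumed a two-sided significance level of *α* = 0.05". On the effect, "we aimed for a slightly lower effect size of *d* = 0.25". On clustering, "we assumed an average group size of *m* = 25 and an ICC of 0.046, which requires 529 participants per arm". Total planned 1250, with 10% attrition.

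**The plan's own figure.** n per arm = 2 × (1.96 + 0.8416)² / 0.25² = 251.2, against the plan's "yielding 251 participants per arm". Design effect = 1 + (25 − 1) × 0.046 = 2.104. Then 251 × 2.104 = 528.1, rounded up to 529. The stated ICC and group size reproduce the stated 529.

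**Assumptions that the protocol does not supply.**
- About 1250 × 0.9 = 1125 pupils analysed, half of them girls, schools of equal size, one timepoint.
- k schools per arm with m pupils each: 25 × 22, 12 × 46 or 6 × 90.
- r, the correlation between a school's effect on its boys and on its girls. The written model corresponds to r = 1.
- First case: the whole ICC of 0.046 lies at school level and applies to each gender.

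**Formulae, with total variance 1.**
- Pupil-level variance of one school's gap, which the written model uses: w = 4(1 − ICC)/m.
- Between-school variance of the true gap, which it omits: τ² = 2 × ICC × (1 − r). For r = 0.9, 0.75 and 0.5 this is 0.0092, 0.023 and 0.046.
- False-positive rate at nominal 5%: 2[1 − Φ(1.96/√((w + τ²)/w))].

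**Worked case, 6 schools per arm and r = 0.5.** w = 4 × 0.954/90 = 0.0424. (0.0424 + 0.046)/0.0424 = 2.085, with square root 1.444. 1.96/1.444 = 1.357, which gives a two-sided rate of 17.5%.

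**All cases, formula (simulation of 40,000 trials in brackets).**

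| Schools per arm × pupils | r = 0.9 | r = 0.75 | r = 0.5 |
|---|---|---|---|
| 25 × 22 | 5.6% (5.5%) | 6.6% (6.5%) | 8.1% (8.0%) |
| 12 × 46 | 6.3% (6.1%) | 8.3% (8.4%) | 11.6% (11.3%) |
| 6 × 90 | 7.6% (7.4%) | 11.5% (11.5%) | 17.5% (17.4%) |

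At r = 1 the formula gives 5.0% and the simulation 4.9% to 5.2%.

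**Half the ICC at school level (0.023).** For r = 0.9 to 0.5 the same formula gives 5.3% to 6.5% (25 per arm), 5.6% to 8.2% (12 per arm) and 6.2% to 11.3% (6 per arm).

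**Separate effects in boys and in girls.** The school intercept covers most of this error. The true variance of one school's mean for one gender is ICC + 2(1 − ICC)/m. The written model uses ICC(1 + r)/2 + 2(1 − ICC)/m. In the worst case (m = 90, r = 0.5) these are 0.0672 and 0.0557, so the standard error is too small by a factor of √1.206 = 1.10. Across the nine cases the factor runs from 1.01 to 1.10.

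**With the gap variance in the error term.** A test using the between-school variance of the gap, not allowed to fall below pupil-level error, with 2k − 2 degrees of freedom, rejected in 2.7% to 4.7% of simulated trials. A plain school-level t-test on the gaps, in a separate set of 16 scenarios, rejected in 4.7% to 6.1%, which is about nominal.

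**The case against.** The strongest reply is that nothing in the protocol shows that the gap varies. A reader might infer it from the pilot, where girls gained in body esteem (Background {6a}) and the smallest effect was in boys (Sample size {14}). That is an average gender difference, which the fixed interaction already models. It says nothing about differences between schools. Mixed-gender delivery does not show it either: boys and girls who share a room and a facilitator may well be affected alike, which points towards r near 1. This part of the reply stands.

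The upper figures also need several unfavourable inputs together: few schools, r = 0.5 and the whole ICC at school level. The protocol ties the ICC to an average group size of 25, which resembles a class, and the model has a class intercept as well. The half-ICC range therefore belongs beside the full one. On the other side, nesting classes within schools suggests more than one class per school. In that event 25 schools of 22 pupils is the less likely layout.

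Gender is absent from the moderators in Objectives {7} and Methods for additional analyses {20b}, and no one-gender claim is announced. That limits the consequence without removing it, because Statistical methods {20a} puts the interaction in the outcome models and names gender as a moderator.

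Finally, random slopes and degrees of freedom are often left to an analysis plan, which is not shown here. But the article does set out the random part and says it is there to reflect the clustering. For this one term it does so only in a special case.

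**Conclusion.** The point holds in conditional form. As written, the gender × group test keeps its 5% level only if the girl-boy gap is identical across schools. If the gap varies, the test is anti-conservative: about 5.5% to 17% over r = 0.9 to 0.5 and 25 down to 6 schools per arm with the full ICC at school level, and about 5% to 11% with half of it there.

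Three stronger readings are not supported:

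- That 6% to 17% is this trial's error rate. It rests on the number of schools, the variation in the gap and the level at which the ICC sits, none of which the protocol gives.
- That the main result is compromised. The arm effect averaged over boys and girls is covered by the school intercept.
- That the separate boys' and girls' effects are seriously misjudged. Their standard errors are too small by at most about 10% under these assumptions.

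The comparison of high and low baseline scorers may share the structure, since baseline level also varies within schools. The protocol does not state the model for it, so it is a secondary matter. This is an inexpensive improvement to the specification and does not undermine the trial.

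**What to change.** In Statistical methods {20a}, add a school-level random slope for gender to every model that contains gender × group. Test the interaction with degrees of freedom based on the number of schools. State in advance that the model reverts to the intercept-only form if the slope variance is estimated as zero. If the baseline-level comparison is to be fitted as an interaction with arm, state its model and consider the same term there.

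The cost is one term in the model formula and no new data. Intervals for the gender contrast will be wider, some fits will be singular, and the test will be somewhat conservative if schools are few (down to 2.7% in the simulations). Recruitment is expected to run to August 2027 (Trial status), so the change can still be specified before the final analysis.

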### Objectives {7}

Evaluate whether participants randomized to receive the intervention show increased media literacy, decreased body dissatisfaction, and/or improvements in secondary outcomes at timepoint 2 and timepoint 3 compared to baseline, relative to participants randomized to the control group.

Assess effects of moderators (socioeconomic status (SES), school type, geographical location) on any observed changes in primary and secondary outcomes in response to the intervention.

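### The stated mixed model uses baseline as both covariate and response and has no group-by-time term, so it estimates two thirds of the mean post-intervention effect and cannot separate Timepoint 2 from Timepoint 3

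*Protocol article*

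**What the plan says.** The section on statistical methods for primary and secondary outcomes {20a} of the protocol article gives one model for each outcome, "including the baseline measure of the outcome, gender, and the interaction between gender (boys vs. girls) and group (intervention vs. control) as fixed effects". Timepoint is then added with its three levels: "as fixed effects, along with timepoint (baseline, immediate post-test, follow-up"). The random part has intercepts for participant and for classes nested in schools. The same section reserves confirmatory inference for the primary outcomes (media literacy and body dissatisfaction) and lists gender among the moderators. A group-by-timepoint term appears neither there, nor under additional analyses {20b}, nor under missing data {20c}.

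Objectives {7} asks for effects "at timepoint 2 and timepoint 3 compared to baseline, relative to participants randomized to the control group". Sample size {14} sets the target: "we aimed for a slightly lower effect size of *d* = 0.25".

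**The concern.** Two features of the listed terms conflict with the objective.

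- The baseline score is on both sides of the equation. At T1 the response is the covariate itself, so after adjustment there can be no group difference at that visit.
- Without group-by-timepoint, the model has one group effect (per gender) that is constant over all three visits, so the forced zero at T1 is averaged in with the effects at T2 and T3.

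The confirmatory estimate would then be too small by a known factor, and its confidence interval would be centred in the wrong place. The trial also asks whether the effect lasts 9–12 months. A single time-constant coefficient cannot answer that, and no contrast of the listed terms recovers the two visit-specific effects.

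**Working it through.** **Inputs.** From Sample size {14}: "two-sided significance level of *α* = 0.05", "80% power (1 − β = 0.80"), d = 0.25, clusters of 25, ICC 0.046, 1250 participants. From {20a}: the model terms quoted above. Not in the document, so assumed: a within-person correlation of 0.6, with 0.4 as the alternative. The protocol gives no figure for the bias.

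**1. The planning value.** n per arm = 2(1.960 + 0.842)²/0.25² = 251.2, which matches "equal allocation to two arms (intervention vs. control), yielding 251 participants per arm". The target is therefore a whole-arm difference of 0.25 SD, and the estimate should be on that scale.

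**2. What the stated model estimates.** With complete data, timepoint is the only fixed effect that varies within a participant. The group coefficient therefore depends only on the participant means:

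M = (Y1 + Y2 + Y3)/3 = Y1/3 + (2/3) × (Y2 + Y3)/2.

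For given variance components the fit is linear in the response. Fitting Y1/3 on a set of covariates that contains Y1 returns a slope of 1/3 on Y1 and zero on everything else, group included. What remains is

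group coefficient = (2/3) × (d2 + d3)/2 = (0 + d2 + d3)/3,

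where d2 and d3 are the baseline-adjusted differences at T2 and T3. This holds for each gender's coefficient and for their average, and the school and class intercepts do not change it.

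**3. Numbers.**

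- d2 = d3 = 0.25: (0 + 0.25 + 0.25)/3 = 0.167.
- d2 = 0.40, d3 = 0.10: (0 + 0.40 + 0.10)/3 = 0.167, the same answer.
- d2 = 0.25, d3 = 0: (0 + 0.25 + 0)/3 = 0.083.

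**4. Standard error.** The residuals of M are two thirds of the residuals of (Y2 + Y3)/2, so the standard error is also multiplied by 2/3 and the test statistic does not change.

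**5. Simulation check.** Maximum-likelihood fits with school and participant intercepts, class level omitted, 50 schools of 25 (1250/25), 12 data sets per row, true effect 0.25 at T2 and T3, group effect averaged over genders:

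| Scenario | As written: estimate (SE), z | T2 and T3 only: estimate (SE), z | Ratio of estimates |
|---|---|---|---|
| Complete, correlation 0.6 | 0.169 (0.029), 5.85 | 0.253 (0.044), 5.85 | 0.667 |
| Complete, correlation 0.4 | 0.169 (0.036), 4.77 | 0.254 (0.054), 4.77 | 0.667 |
| 10% missing at T3, correlation 0.6 | 0.159 (0.031), 5.22 | 0.242 (0.047), 5.23 | 0.656 |

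With a true 0.25 at T2 and 0 at T3 (complete data, correlation 0.6), the model as written returned 0.088. A model with group-by-time returned 0.260 at T2 and 0.004 at T3.

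**6. Effect on the interval.** At correlation 0.6, an estimate at its expected value gives 0.167 ± 1.96 × 0.029 = 0.110 to 0.224, which excludes the true 0.25. With T2 and T3 only it gives 0.25 ± 1.96 × 0.044 = 0.164 to 0.336.

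**The case against.** The best defence is that {20a} is prose, not code. The parenthesis after timepoint may only list the study visits, and the objectives and the outcomes section make the intended comparisons clear. An analysis plan that is not shown might fit group-by-time. This has some force: the diluted estimate follows from fitting the listed terms literally and is not a certain outcome. It does not remove the point. The section prints an explicit model with baseline in both roles, and that model conflicts with the stated objective. This is a misstatement, not detail left for later.

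Some stronger readings are tempting but are not supported.

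- *A one-third loss of power.* Putting 0.167 into the sample-size formula with the full SD gives about 49% power, against about 82% at 0.25 (562.5 evaluable per arm, design effect 2.104). That is the wrong calculation, because the standard error shrinks too (step 4).
- *No overall group effect.* Group is named only inside the gender interaction, but naming an interaction commonly implies its lower-order terms. Even read literally, the two gender-specific effects can be averaged. The contrast needs naming; it is not unobtainable.
- *Underpowered gender-specific tests.* Half of 562.5 per arm with 12.5 per class gives a design effect of 1 + 11.5 × 0.046 = 1.529, an effective 184 per arm and about 67% power. This ignores the baseline adjustment in the model. At an assumed correlation of 0.6 the variance is multiplied by 0.64, z rises from 2.40 to 3.00 and power is about 85%, if the reduction also holds at cluster level. Nor does the protocol make the gender-specific coefficients the confirmatory test.
- *Inflated type I error from intercept-only school effects.* This concerns a model with group-by-time that the protocol does not state, and it depends on a correlation of school effects over time that the document does not give.
- *An unsuitable effect size.* "To estimate effect sizes, we will calculate partial eta squared" is a reporting choice, in line with how the pilot results are given, and not an error.

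**Conclusion.** The point holds as a fault in the stated model. As written, and with complete data, the group effect is exactly two thirds of the mean of the T2 and T3 effects: 0.167 SD for a true 0.25 SD at both visits. That ratio does not depend on the assumed within-person correlation. It was 0.656 in the simulation with 10% missing at T3. The standard error falls in about the same proportion, so the test is largely unaffected, while the estimate and its interval are biased towards zero. The interval in step 6 does depend on the assumed correlation and on leaving out the class level. Whatever the correlation, the model gives no separate T2 and T3 effects and so cannot meet the first objective. Because this model carries the confirmatory inference, the text must be corrected.

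**What to change.** Rewrite the model paragraph in {20a} in one of two equally valid ways.

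1. Use only the T2 and T3 scores as responses, with the baseline score as covariate and group, time and group-by-time as fixed effects.
2. Keep all three timepoints as responses, drop the baseline covariate and estimate group-by-time with the baseline mean held common to both arms. This is closer to the comparison with baseline in the objectives.

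In either case, name the adjusted group differences at T2 and at T3, overall across genders and with 95% confidence intervals, as the confirmatory estimates. Use gender-by-group only in the moderator analyses, where {20a} already lists gender.

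The cost is one paragraph and the analysis script, with no new data. It is best done before the interim analysis of T2 data described in {21b}, so that the model is not changed with results in view. Recruitment is expected to run to August 2027.
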